**Fig. 1 Fig1:**
[figure not shown]
Study flow diagram showing the key components of the intervention

### N = 87

Where P1 = HIV Prevalence in 2012 = 0.189 & P2 = HIV Prevalence in 2014 = 0.163 [2]. P̃ = (P1 + P2)/2 = 0.176. Z1 – α/2 = standard error when α = 0.05 (95% confidence interval) = 1.96, and Z1 – β = standard error associated with power = 0.842 (β = 0.20) and Power (1 – β) = 80%.

As participants are nested within in villages, a potential design effect needs to be considered. The assumed number of participants per hospital/NGOs is 20, and an intra-cluster correlation coefficient of 0.05 can be expected. This would result in a design effect = 1 + (m-1) × ICC = 1 + (20–1) × 0.05 = 2. Based on the above formula, the required minimum sample size for each group, n is **174.** To factorise in 10% attrition (32), the total required per group is **192**; hence, a total of **384** patients will be required for the sample in both groups.

Figure 2 below shows a schematic diagram for the development of the intervention module used in this study. The module will be developed through the process of consultation with a group of experts who will include one professor of statistics, one expert in behavioural intervention, one senior medical doctor, and one HIV/AIDS specialist (Fig. 2). The mobile based SMS counselling intervention aims to increase the knowledge, attitude, and practices of patients concerning HIV/AIDS prevention in Malaysia. The SMS will be developed by the researcher based on FGDs and a literature review. It uses informal language and will be sent weekly on Friday, which is a holiday. These factors have been shown to have an impact and positively affect the message acceptability when using SMSs for sexual health promotion [14, 15]. Mobile phones and the Internet are popular everywhere in Malaysia, and are well-liked by people, so the study aims to determine whether they would be effective and improve patient’s knowledge, attitude, and practices concerning HIV/AIDS prevention.

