## Methods/design

The main objective of this study is to develop, implement, and assess the effectiveness of the mobile SMS counselling intervention to improve the knowledge, attitude, and practices of HIV/AIDS patients concerning HIV/AIDS prevention in Malaysia. The specific objectives are given below: to assess the patients initial response to mobile SMS counselling intervention in terms of acceptability, feasibility, and sustainability; to develop mobile SMS counselling intervention for HIV/AIDS prevention; to identify factors associated with the willingness to read text messages on HIV/AIDS prevention in Malaysia; to determine the socio-demographic and environmental factors, level of knowledge, attitude, and practices of patients on HIV/AIDS prevention; to develop and implement a Mobile SMS counselling HIV/AIDS prevention intervention to improve the knowledge, attitude, and practices of HIV/AIDS patients; to determine the association among the socio-demographic factors and environmental factors with knowledge, attitude, and practices of HIV/AIDS patients about HIV/AIDS prevention at the baseline and post intervention; to compare the mean scores for knowledge, attitude, and practices among HIV/AIDS patients between the intervention and the control group at the baseline and post intervention (within group and between groups); and to evaluate the effectiveness of Mobile SMS counselling intervention among HIV/AIDS patients to improve the knowledge, attitude, and practices concerning HIV/AIDS.

The hypotheses are given below: There is an association between the willingness to read text messages and HIV/AIDS patients in Malaysia; there is no significance in the socio-demographic and environmental factors, level of knowledge, attitude, and practice of patients concerning HIV/AIDS prevention; there is an association between the social-demographic and environmental factors, and the knowledge, attitude, and practices of HIV/AIDS patients concerning HIV/AIDS prevention at baseline and post-intervention; there is a significant difference in the mean scores for the knowledge, attitude, and practices of HIV/AIDS patients between the intervention and control group at the baseline and post-intervention (within and between groups), and the application of Mobile SMS counselling intervention to improve the impact of the HIV/AIDS prevention knowledge, attitude, and practices among patients, between the intervention and the control group.

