The research questions are given below: What are the socio-demographic and environmental factors associated with the knowledge, attitude, and practice of HIV/AIDS patients? What is the difference in the mean scores for the knowledge, attitude, and practices of HIV/AIDS patients concerning HIV/AIDS prevention for the intervention and control groups? And what is the impact of Mobile SMS counselling intervention on the knowledge, attitude, and practices of HIV/AIDS patients?

This is a mixed methods research. The first phase will be a qualitative study to develop a mobile SMS counselling intervention concerning the knowledge, attitude, and practices of patients concerning HIV/AIDS prevention, while the second phase will be a quantitative study to implement and evaluate the effectiveness of a mobile-based counselling intervention concerning the knowledge, attitude, and practices of patients in respect of HIV/AIDS prevention. Three focus group discussions (FGDs) will be conducted with 6 male HIV/AIDS patients with FGDs, 6 female HIV/AIDS patients with FGDs, 10 community leaders from a village with FGDs, and three in-depth interviews (IDIs) will be conducted with 3 HIV/AIDS patients. The second phase, the cluster randomized clinical trial, will be carried out for approximately 12 months from September 2019 to July 2020. The hospital/NGOs (or cluster) will be the unit of randomization, and an equal number of hospitals/NGOs will be randomized to one of the two arms. This phase includes a Community trial and pre- and post-assessment through face-to-face interviews using a semi-structured questionnaire (Fig. 1). The study population will be HIV/AIDS patients in the Kuala Terengganu and Kuala Nerus districts of Malaysia. A complete list of HIV/AIDS patient registration will be collected from the Hospitals/NGOs in Kuala Terengganu and Kuala Nerus districts from January 2018 to March 2019. The sampling units will be individual patients who are admitted into the Hospital/NGOs between January 2018 and March 2019 and who are eligible according to the inclusion criteria for this study. The criteria for inclusion in this study include all persons diagnosed with HIV ≥ 18 years of age. Patients excluded from this study are those patients who are HIV positive but diagnosed with psychiatric disorders and are mentally incapacitated. The sample size estimation formula for hypothesis testing of the two-group comparison is used [13]:

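### The sample size rests on a calendar change in HIV prevalence, which is not a trial outcome and does not vary among participants, so 384 and its 80% power have no link to the knowledge, attitude and practice outcomes

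*Protocol article*

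**What the plan says.** The protocol article, Methods/design, introduces the calculation thus: "The sample size estimation formula for hypothesis testing of the two-group comparison is used". The printed expression is the usual one for comparing two proportions. Its inputs, given below Fig. 1, are "Where P1 = HIV Prevalence in 2012 = 0.189 & P2 = HIV Prevalence in 2014 = 0.163", with a mean of 0.176. The multipliers are "standard error when α = 0.05 (95% confidence interval) = 1.96" and "standard error associated with power = 0.842 (β = 0.20) and Power (1 – β) = 80"%. The result is N = 87.

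For clustering the article adds: "The assumed number of participants per hospital/NGOs is 20, and an intra-cluster correlation coefficient of 0.05 can be expected". The design effect is rounded to 2, giving 174 per group. A 10% allowance for attrition gives 192 per group and 384 in total. The number of hospitals/NGOs is not given.

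On who is enrolled: "The criteria for inclusion in this study include all persons diagnosed with HIV ≥ 18 years of age". On what is compared, one objective is "to compare the mean scores for knowledge, attitude, and practices among HIV/AIDS patients between the intervention and the control group". The Results paragraph of the abstract likewise names knowledge, attitude and practices as the main outcomes, at immediate follow-up and at 3 months. The planned tests are a t-test, a chi-square test and analyses of variance, with a logistic model for associated factors.

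**The concern.** The two proportions in the calculation are not the expected results of the two arms on any outcome. They are prevalences of HIV in two years. Among participants who all have HIV the prevalence is 100% in each arm at each visit, so no between-arm difference in it can arise. The 2.6-point fall from 2012 to 2014 is a change over time and does not predict what SMS counselling does to a knowledge, attitude or practice score.

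At stake is the only justification given for 384. A reader will take the 80% power to apply to the trial's question. Nothing in the article supports that, and it gives no difference, SD or proportion for any knowledge, attitude or practice outcome. There is thus no valid advance statement of what the trial can detect.

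**Working it through.** **1. Does 87 follow from the printed inputs?**

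Inputs (Methods/design): P1 = 0.189, P2 = 0.163, mean 0.176, multipliers 1.96 and 0.842. Formula, with the square roots read in the standard way:

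n = {1.96·√[2·P̃(1−P̃)] + 0.842·√[P1(1−P1) + P2(1−P2)]}² / (P1−P2)²

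- 2 × 0.176 × 0.824 = 0.29005; root 0.53856; × 1.96 = 1.0556
- 0.189 × 0.811 + 0.163 × 0.837 = 0.28971; root 0.53825; × 0.842 = 0.4532
- (1.0556 + 0.4532)² = 2.2764
- (0.026)² = 0.000676
- n = 2.2764 / 0.000676 ≈ 3,367 per group

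This is about 39 times 87 (3,367 / 87 = 38.7). Other readings do not recover 87 either:

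| Reading | n per group |
|---|---|
| One-sided | 2,652 |
| Two-sided, continuity correction | 3,443 |
| Unpooled variance | 3,364 |
| Literal readings of the typeset roots | about 980 to 1,030 |

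The later steps do follow from 87: 87 × 2 = 174, and 174 × 1.10 = 191.4, rounded up to 192; 2 × 192 = 384.

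**2. Would correct arithmetic repair the justification?**

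No. Carrying 3,367 through the unrounded design effect, 1 + 19 × 0.05 = 1.95, gives 6,566, and 6,566 / 0.9 gives 7,296 per group. That figure would still concern a change in prevalence between years.

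**3. What can 384 detect on a mean score?**

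Inputs: 192 per group × 0.9 ≈ 173 analysed per group; K clusters in all, equally split; m = 346 / K per cluster; two-sided 5%, 80% power, no baseline adjustment.

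- Design effect DE = 1 + (m − 1) × ICC
- Effective size per group n_eff = 173 / DE
- Detectable difference in SD units d = (t₀.₉₇₅ + t₀.₈₀) × √(2 / n_eff), with K − 2 degrees of freedom

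For K = 20 and ICC 0.05: m = 17.3; DE = 1.815; n_eff = 95.3; d = (2.101 + 0.862) × √(2 / 95.3) = 0.429. With normal multipliers it is 0.406.

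K = 20 is an assumption, from 384 / 20 = 19.2. Varying K at ICC 0.05:

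| K | m | DE | n_eff | d (SD) |
|---|---|---|---|---|
| 20 | 17.3 | 1.82 | 95.3 | 0.43 |
| 16 | 21.6 | 2.03 | 85.2 | 0.46 |
| 12 | 28.8 | 2.39 | 72.3 | 0.52 |
| 8 | 43.3 | 3.11 | 55.6 | 0.64 |
| 6 | 57.7 | 3.83 | 45.1 | 0.78 |

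The ICC of 0.05 is not tied to any score. Varying it at K = 20:

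| ICC | DE | n_eff | d (SD) |
|---|---|---|---|
| 0.01 | 1.16 | 148.8 | 0.34 |
| 0.05 | 1.82 | 95.3 | 0.43 |
| 0.10 | 2.63 | 65.8 | 0.52 |

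**The case against.** The first defence is that an article condenses a fuller protocol. That does not help here, because the calculation is printed from formula to total and its inputs are labelled. The defect is in what is stated.

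A second defence is that prevalence is never called an endpoint. That is true. A reader might infer that the trial means to test HIV prevalence, but the article uses it only as a sizing input. The fault is that the input is unrelated to any outcome.

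A third is that a two-proportion formula suits a trial that plans a chi-square test. This stands in part: a dichotomised knowledge, attitude or practice outcome could be sized that way. The formula type is not the error; the proportions entered are.

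A fourth is that the result can be read whatever the planning. This also stands. A reader might infer that a non-significant score difference would be uninterpretable, but its confidence interval would still show which effects fit the data. What is lost is the reason for 384 and the advance statement of its power.

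**Conclusion.** The concern holds. The stated 80% power refers to a quantity that is constant among participants and is not an outcome, and 384 is not supported even for that quantity, since the printed inputs give about 3,367 per group and not 87.

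A reader might go further and conclude that 384 is too few. The article does not support that: without a named primary outcome and a difference worth detecting, neither adequacy nor inadequacy can be shown. What can be said is that 384 patients would detect about 0.43 SD under 20 clusters and ICC 0.05, and between 0.34 and 0.78 SD over the ranges tried. These figures assume equal cluster sizes, 10% attrition and no baseline adjustment. The cluster number and the ICC for a score are assumptions, so no single value should be taken as the trial's detectable difference.

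**What to change.** Withdraw the prevalence-based power statement. Name one knowledge, attitude or practice score and one timepoint as primary; the article lists two follow-up times without ranking them. Then state what the sample can detect, for example:

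*With 384 patients in [K] hospitals/NGOs, 10% attrition and ICC [value], the trial has 80% power for a between-arm difference of about [d] SD in [primary score] at [timepoint].*

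Fill K with the actual number of hospitals/NGOs and show a range of ICCs. Convert d to score points once an SD is known from pilot or baseline data. If the primary outcome is dichotomised, give the two-proportion equivalent with expected proportions for that outcome. The same rewrite removes the 87.

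The restatement costs wording only and admits that only moderate or larger effects are detectable. It describes 384 and does not by itself justify it. If the sponsor judges a smaller difference important, the number of patients or clusters would have to be reconsidered. As an illustration with normal multipliers, 0.3 SD needs 175 per group; × 1.95 gives 342; / 0.9 gives 380, or 760 in total.

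### N = 87 per group does not follow from the printed formula and inputs, which give about 3,368; the 384 built on it has no valid justification as written

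*Protocol article*

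**What the plan says.** The Methods/design section introduces the calculation thus: "The sample size estimation formula for hypothesis testing of the two-group comparison is used". The formula printed next is the usual one for two proportions, with (P1 − P2) squared in the denominator. Below Fig. 1 the article gives the result, N = 87, and the inputs:

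- "Where P1 = HIV Prevalence in 2012 = 0.189 & P2 = HIV Prevalence in 2014 = 0.163", with a mean of 0.176
- "standard error when α = 0.05 (95% confidence interval) = 1.96"
- "standard error associated with power = 0.842 (β = 0.20", that is, 80% power.

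Allocation is 1:1 by cluster: "an equal number of hospitals/NGOs will be randomized to one of the two arms". With 20 participants per hospital or NGO and an intra-cluster correlation of 0.05, the article gives a design effect of 2. It continues "Based on the above formula, the required minimum sample size for each group, n is" 174, then allows 10% for attrition to reach 192 per group and 384 in total. The Abstract repeats the 384.

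**The concern.** A difference of 2.6 percentage points between proportions near 0.18 normally needs thousands of patients per group, so 87 is implausible on sight. Formula, inputs and result all stand on the page, so the figure can be checked without any outside source. This is the only power statement in the article, and every later sample-size figure depends on it. If it is wrong, the 384 has no stated basis, and readers who use the 80% figure to interpret the results will be misled.

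**Working it through.** **Inputs** (all from the sample-size text in Methods/design): P1 = 0.189, P2 = 0.163, P̄ = 0.176, P1 − P2 = 0.026, z = 1.96 and 0.842.

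**Formula.** N = [1.96·√(2P̄(1−P̄)) + 0.842·√(P1(1−P1) + P2(1−P2))]² / (P1−P2)²

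- First term: 1.96 × √(2 × 0.176 × 0.824) = 1.96 × √0.290048 = 1.0556
- Second term: 0.842 × √(0.189 × 0.811 + 0.163 × 0.837) = 0.842 × √0.28971 = 0.4532
- Numerator: (1.0556 + 0.4532)² = 1.5088² = 2.2764

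**Reproducing the plan's figure.** Dividing by the unsquared difference gives 2.2764 / 0.026 = 87.55, truncated to 87.

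**Following the printed formula.** Dividing by 0.026² = 0.000676 gives 3,367.5, so 3,368 per group. The ratio to the stated figure is 3,367.5 / 87 = 38.7.

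**Other readings of the same formula and inputs**

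| Variant | N per group |
|---|---|
| Unpooled variance | 3,364 |
| Continuity correction | 3,443 |
| One-sided test | 2,652 |
| Literal readings of the displaced square roots | about 980 to 2,864 |
| Square roots dropped altogether | 976 |

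None comes near 87, so the broken root signs do not explain it.

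**What inherits the error.** 87 × 2 = 174; 174 × 1.10 = 191.4, raised to 192; 2 × 192 = 384. With the unrounded design effect, 1 + 19 × 0.05 = 1.95, the stated inputs need 3,367.5 × 1.95 = 6,567 per group before attrition.

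**Power for 0.189 v 0.163 at 87 per group.** z = (0.026 × √87 − 1.0556) / √0.28971 = (0.2425 − 1.0556) / 0.5382 = −1.511, which gives 6.5%, or 7.3% if rejections in the wrong direction are counted. The clustered numbers come to much the same: 174/1.95 = 89 effective patients gives 6.6%, and 192/1.95 = 98 gives 6.9%. Even if clustering is ignored, 192 per group gives 9.8%.

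**What about 87 effective patients per arm can detect at 80% power**

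- A score compared at one time point: (1.96 + 0.842) × √(2/87) = 0.42 SD. With 192/20, or about 10 clusters per arm, t quantiles on 18 degrees of freedom replace the normal ones: (2.101 + 0.862) × √(2/87) = 0.45 SD.
- A proportion, solving the same formula for N = 87 from a base of 0.189: upwards 0.379 (19 points), downwards 0.052 (13.7 points).

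**The case against.** The strongest objection concerns what the 7% means. A reader might infer that the trial has 7% power and that a null result would be uninformative. The document does not support that. The two proportions are HIV prevalences in 2012 and 2014, whereas every participant already has HIV and the outcomes are knowledge, attitude and practice, compared as mean scores. The trial will never produce a result on 0.189 v 0.163. Power for its real outcomes depends on effect sizes and standard deviations that the article does not give, and it could be well above 7%. This objection stands, and it confines the 7% to the named contrast. It does not rescue the calculation: no other effect size is offered, so nothing else supports the 384.

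It may also be said that 384 has another origin. The familiar precision formula for one proportion, 1.96² × 0.25 / 0.05², gives 384.16. But the article derives 384 step by step from 87, and a precision formula for one proportion does not size a two-arm comparison.

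The unsquared denominator is an inference about the cause. A one-proportion precision formula with a margin of 0.08 would also give 87.05, but the article mentions no such margin. That the figure is wrong does not depend on how it arose.

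Finally, a full protocol or analysis plan could add a proper calculation. It could not make this printed result agree with this printed formula.

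**Conclusion.** The point holds as a contradiction between the article's own formula, inputs and result. N should read about 3,368 per group, not 87, and about 6,567 with design effect 1.95. The most likely cause is an unsquared denominator. The figures 174, 192 and 384 inherit the error, and power for 0.189 v 0.163 is about 7%, not 80%. These results need no assumption beyond the article's own inputs.

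The consequence is that 384 has no valid justification as written. Whether it is too small for the score outcomes cannot be decided from the document. The 0.42 SD figure assumes 20 patients per cluster, an intra-cluster correlation of 0.05, equal cluster sizes and no gain from baseline adjustment.

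**What to change.** Withdraw N = 87 and the 80% power claim for 0.189 v 0.163. Replace them with a statement of what 384 patients can detect on a knowledge, attitude or practice score, naming the score and its assumed standard deviation: roughly 0.42 SD at 80% power with about 87 effective patients per arm, and about 0.45 SD once some 10 clusters per arm are allowed for. Beside it, say what difference on that score would matter, since a detectable effect worked back from 384 does not answer that.

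If a proportion is kept, make it one that the trial measures and give the detectable difference in both directions (from a base of 0.189, for example, up to about 0.38 or down to about 0.05).

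The cost is one rewritten paragraph and a less favourable stated effect. The restatement itself needs no extra patients; if the difference that matters proves smaller than the detectable one, the sample size would have to be reconsidered.

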**Fig. 2 Fig2:**
[figure not shown]
Schematic diagram of the development of the intervention module

The control group patients will not receive any SMS during the study periods, but the usual information received from the mass media (newspaper, TV, Radio) or any campaign for HIV/AIDS prevention. However, they will receive the SMS counselling intervention about HIV/AIDS after data collection.

The Statistical Package for Social Science (SPSS) version 22 will be used to analyse the data. Data will be collected, checked, cleaned, and data entry will be conducted carefully and successfully. Factors with a statistically significant association with the socio-demographic and environmental variables on HIV/AIDS prevention knowledge, attitude, and practices will be identified at the baseline, immediate post intervention, and after 3 months follow up in the logistic model (ρ-value of 0.05) controlling for other variables. To determine the significant difference between the intervention and the control groups, a t-test and chi-square test will be used. To identify the impact of two different interventions, 2-way repeated measure ANOVA and one-way ANOVA will be used.

The main findings are given below: development of mobile SMS based counselling intervention for prevention of HIV/AIDS with FGDs; identification of implementation process for mobile SMS based counselling intervention for prevention of HIV/AIDS patients; development of tools for measuring the effectiveness of Mobile SMS based counselling intervention for prevention of HIV/AIDS patients; development of an effective intervention for HIV/AIDS patients in a low resource setting to improve the knowledge, attitude, and practices concerning HIV/AIDS prevention, and assessment of the effectiveness of a mobile SMS based counselling intervention programme on the HIV/AIDS prevention knowledge, attitude, and practices of HIV/AIDS patients.

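### Socio-demographic and environmental factors are declared identified at an unadjusted p of 0.05 for three outcomes at three time points; reporting them as exploratory estimates would be safer and cheap

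*Protocol article*

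**What the plan says.** The statistical analysis paragraph (Methods/design, after Fig. 2) gives a selection rule: "Factors with a statistically significant association with the socio-demographic and environmental variables on HIV/AIDS prevention knowledge, attitude, and practices will be identified". The same sentence fixes the time points and the threshold, so that such factors "will be identified at the baseline, immediate post intervention, and after 3 months follow up in the logistic model (ρ-value of 0.05) controlling for other" … The outcomes are knowledge, attitude and practices.

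The same question appears in two other places under Methods/design:

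- **Hypotheses.** One states that "there is an association between the social-demographic and environmental factors, and the knowledge, attitude, and practices of HIV/AIDS patients concerning HIV/AIDS prevention at baseline and" after the intervention. It stands in the same list as the between-group hypothesis, with no order of importance. The statement just before it reads "there is no significance in the socio-demographic and environmental factors, level of knowledge, attitude, and practice of patients concerning HIV/AIDS prevention".
- **Research questions.** The first of three is "What are the socio-demographic and environmental factors associated with the knowledge, attitude, and practice of HIV/AIDS patients".

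The Abstract (Results) names the main outcomes as the differences in knowledge, attitude and practices. The article does not say how many factors will be examined.

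**The concern.** The rule turns each p-value below 0.05 into a named factor, and it is applied to three outcomes at three time points. A 5% error rate per test is then no longer a 5% error rate per factor, still less for the whole set. A report that followed the wording could present chance findings as determinants of HIV prevention knowledge, attitude or practice.

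A second problem comes from testing each visit separately. A factor with a constant association can be significant at one visit and not at another through sampling variation alone. In a trial with a baseline and two assessments after an intervention, such a pattern is easily read as the factor gaining or losing importance after the SMS. Adjusting p-values would not cure this, because a difference between two significance verdicts is not a test of change.

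**Working it through.** **Inputs from the article**

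- Threshold: 0.05 per test (statistical analysis paragraph). Sidedness is not stated; two-sided is assumed.
- Outcomes: 3. Time points: 3.
- No error rate over the set of tests is stated, so there is no figure of the plan to reproduce.

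**Assumptions, because the article does not give them**

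- Each outcome is tested separately at each time point: 3 × 3 = 9 tests per factor.
- The nine test statistics of one factor share a common correlation between 0 and 0.8. Different factors are independent.
- The number *k* of factors with no true association. The text speaks of variables in the plural and of controlling for others, so more than one factor is examined, but how many of them are null is unknown.

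**Step 1. One null factor, independent tests**

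1 − 0.95⁹ = 1 − 0.630 = 0.370, or 37%.

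**Step 2. One null factor, correlated tests**

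The chance that at least one of nine correlated z-statistics exceeds 1.96 in absolute value is:

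| Correlation | Chance of being named at least once |
|---|---|
| 0 | 37% |
| 0.3 | 33% |
| 0.5 | 27% |
| 0.8 | 17% |

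**Step 3. Several null factors**

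With independent factors the chance is 1 − (1 − p)ᵏ, where p is the unrounded one-factor value (0.3698 at correlation 0, 0.1655 at 0.8).

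- k = 3, correlation 0: 1 − 0.6302³ = 0.75.
- k = 3, correlation 0.8: 1 − 0.8345³ = 0.42.
- k = 5: 60% to 90%.

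The expected number of false associations is 9 × k × 0.05: 0.45 for one null factor, 1.35 for three and 2.25 for five. Correlation does not change these expectations.

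**Step 4. If there is only one test per outcome**

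The text refers to the logistic model in the singular. If each outcome gave one test per factor instead of three, the independent-test figures would be 1 − 0.95³ = 14% for one null factor and 1 − 0.95⁹ = 37% for three.

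**Step 5. Disagreement between visits**

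Take a real, constant association tested with 80% power at each visit. This power is chosen for illustration; the article states none for this analysis. With independent tests, the three visits fail to agree on significance with probability 1 − 0.8³ − 0.2³ = 1 − 0.512 − 0.008 = 0.48. With correlation 0.5 the figure is 34%, and with 0.8 it is 21%.

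**The case against.** - **The analysis is not called confirmatory.** This stands. A reader might infer that status from the hypothesis list and the first research question. However, the article does not rank its hypotheses, the Abstract names the differences in knowledge, attitude and practices as the main outcomes, and the list of main findings that closes Methods/design leaves out associated factors. An unadjusted 0.05 is common for a secondary, descriptive aim of this kind.
- **Multiplicity is usually left to the SAP or the full protocol, and only a condensed article is shown.** This stands against any complaint that an adjustment is missing. It does not remove the point, which concerns a rule that the article states: factors are identified at 0.05, at each time point.
- **The size rests on assumptions.** This stands in part. A reader might conclude that a false factor is almost certain. That needs many factors, most of them null, and the article supports neither premise. At three null factors and strong correlation the chance is 42%, which is below one half. The one-factor figure does not depend on the number of factors, but it does depend on separate testing.
- **The two factor hypotheses need not contradict each other.** This stands. A reader might take one as the negation of the other, so that a single significant result confirms one and refutes the other. The statement of no significance is too garbled for that: it lists factors and levels side by side without stating a relation between them. The article gives no such decision rule.
- **No objective asks whether associations change over time.** This is true, and it limits the visit-to-visit problem to a risk of misreading. The risk is still there, because the rule produces separate results by visit.

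**Conclusion.** The concern holds as a minor point about how factor findings are selected and worded. Under separate testing by outcome and time point, a null factor is named at least once with probability of about 17% to 37%, against 5% for a single test. With three null factors the chance is about 42% to 75%. These ranges assume two-sided tests, correlation from 0.8 down to 0 within a factor and independence between factors; three is an assumed count. Fewer separate tests would lower the figures.

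The comparison of SMS with control is unaffected, and so is the sample size. The documents do not show that the factor analysis is confirmatory, that a false factor is almost certain, or that the hypotheses formally contradict each other.

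**What to change.** **Hypotheses (Methods/design).** Replace the two factor statements with one exploratory objective: to describe how socio-demographic and environmental factors relate to knowledge, attitude and practices.

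**Statistical analysis paragraph.** Replace the rule that identifies factors at p 0.05 with wording such as: *Associations with socio-demographic and environmental factors are exploratory. The factors are prespecified. Estimates with 95% confidence intervals are reported for all of them, from models that account for repeated measures within patients and for clustering by hospital/NGO. Any change in a factor's association over time is judged only by a factor-by-time term.*

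The patient and cluster terms are needed because patients are assessed repeatedly and hospitals/NGOs are randomised. The sample size section itself allows for an intra-cluster correlation of 0.05. Without these terms the confidence intervals need not be valid.

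**Optional.** If the sponsor wants to name factors, apply Holm or false discovery rate control across factors and outcomes. This is a trade-off, since a weak true factor is then less likely to be declared.

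**Cost.** Wording only, with no new patients or data. Factor findings become hypothesis-generating.
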